### Randomisation and treatment allocation

Employees can not be randomly assigned to OPs trained in the intervention or OPs not trained in the intervention because the OPs and employees are bound to each other by the company. It is also impossible to train all OPs and to let them randomly apply the intervention or CAU to employees because of the risk of contamination. Therefore, randomisation occurs at the level of the OP. OPs who have given their consent to participate in the study are randomly assigned to the intervention group or the control group. To ensure a good contrast between these two groups, OPs in the intervention group are specifically asked not to talk about the intervention with OPs in the control group. Additionally, the OPs in the intervention group have two feedback meetings to discuss the application of the intervention with each other.

A computerised random allocation sequence for randomising the OPs is developed by an independent researcher. When all OPs are recruited, the independent researcher, who is blind to the identity of the OPs, uses the allocation sequence to randomise the OPs. After this, the allocation of the OPs can not be changed and the independent researcher informs the researchers about the allocation of the OPs. The allocation of employees follows from the allocation of their OP. Employees with an OP in the intervention group are automatically allocated to the intervention group and employees with an OP in the control group are automatically allocated to the control group.

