### Recruitment of occupational physicians

Recruitment of OPs takes place in collaboration with ArboNed, one of the largest Occupational Health Services (OHS) in the Netherlands. OPs participating in this study are employed at this OHS and are affiliated with companies of different sizes, in different sectors and in different parts of the Netherlands. Company size ranges from less than five employees up to more than a 1000 employees in different sectors, for instance industry, education, health care, and customer services. All regions in the Netherlands, except the south, are participating in the study. OPs are excluded when they: 1. have an upcoming retirement, resignation, sabbatical, or pregnancy leave, or 2. are unable to use the internet and/or email.

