### Sample size

For the power calculation, recurrent sickness absence days are considered the primary outcome measure. To calculate the sample size, administrative data from the sickness absence registry of the OHS was used. From 2001 to 2007, recurrent sickness absence days among employees, who had returned to work after a period of sickness absence because of CMDs, were registered. For the power calculation, only recurrent sickness absence days of the first recurrence episode until 1 year later were used to approximate the 1 year follow-up of the present study (N = 4443). The variance in recurrent sickness absence days at the level of the OP was taken into account.

During the above-mentioned period, the mean days of recurrent sickness absence was 68.5 (standard deviation is 119.6). The target of the present study is to reduce the recurrent sickness absence days with 20%, i.e. an average of 12.7 recurrent sickness absence days per employee per year. The OPs in this OHS's dataset were randomly divided into two groups. One group was called "the intervention group" from which 20% of the recurrent sickness absence days was subtracted to create the difference between the intervention and control group and to calculate an effect size.

For a decrease of 12.7 recurrent sickness absence days per employee during 1 year at alpha = 0.05 and ICC = 0.05, 50 OPs, each providing five employees, need to be included in each group (the intervention and control group) [29]. The five employees must be viewed as the average number per OP. For this multilevel power calculation, an effect size of 0.18 was taken into account. This effect size was calculated by using a logtransformation on the data to create a normal distribution and subsequently by dividing the difference in mean days of recurrent sickness absence between the intervention and control group (difference is 0.25) by the standard deviation (standard deviation of difference is 1.4). To include the effect size in the multilevel power calculation, it had to be transformed to a correlation coefficient, which resulted in a correlation of 0.09 [30].

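### The article describes no use of the OP-linked absence history in allocation or as a prespecified covariate, which gives up a modest amount of precision

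*Protocol article*

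**What the plan says.** **Allocation.** Under Randomisation and treatment allocation, the article states that "A computerised random allocation sequence for randomising the OPs is developed by an independent researcher", and that "When all OPs are recruited, the independent researcher, who is blind to the identity of the OPs, uses the allocation sequence to randomise the OPs". No stratification, matching, minimisation or constraint is named.

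**OP diversity.** Recruitment of occupational physicians describes the OPs as "affiliated with companies of different sizes, in different sectors and in different parts of the Netherlands".

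**Existing data.** Under Sample size, "To calculate the sample size, administrative data from the sickness absence registry of the OHS was used". It covers recurrent absence from 2001 to 2007 and 4443 observations. OPs are units in it: "The variance in recurrent sickness absence days at the level of the OP was taken into account", and "The OPs in this OHS's dataset were randomly divided into two groups".

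**Analysis.** Statistical analyses plans multilevel regression with employees nested in OPs. Its only stated adjustment rule is to compare baseline characteristics between the arms and control for those that differ significantly. No OP-level predictor is named.

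**The concern.** Balancing clusters is usually hard because they enter one at a time, or because nothing about their outcome level is known beforehand. Neither obstacle is evident here. All OPs are in hand before the sequence is applied, and the registry that will help supply the primary outcome already held OP-linked data on a closely related quantity.

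The stated covariate rule does not make up for this. It picks covariates by a significance test of differences that, under sound randomisation, arise by chance, and not by how well they predict absence. The baseline characteristics it tests are also collected from employees after their OP has been allocated. OPs know their arm (Blinding) and choose whom to invite, and Methodological considerations says that selection cannot be excluded. OP history from before the trial cannot be affected by allocation. It would not cure selection, but it is a covariate without that weakness.

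What is at stake is the between-OP part of the standard error of the primary comparison.

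**Working it through.** **Inputs from Sample size:** ICC 0.05; 50 OPs per arm with five employees each; alpha 0.05 (taken as two-sided, since sidedness is not stated); standardised effect 0.18 on the log scale.

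**The plan's own figures.** The effect size reproduces: 0.25/1.4 = 0.179. So does the correlation: 0.18/sqrt(0.18² + 4) = 0.090. The article states no power. With a design effect of 1 + 4 × 0.05 = 1.20, 250 employees per arm give 45.1% two-sided power, which is the baseline below. That shortfall is a separate matter.

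**Share of variance that OP history can reach.** The variance of an OP mean is 0.05 + 0.95/5 = 0.24. The between-OP share is 0.05/0.24 = 20.8%, the ceiling on any gain from OP-level information.

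**Chance imbalance.** Under unrestricted allocation, the difference between arms in mean OP effect has SD sqrt(2 × 0.05/50) = 0.045. The total standard error is sqrt(2 × 0.24/50) = 0.098 and already contains it.

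**Gain from history.** Let R² be the share of between-OP variance explained. The variance of an OP mean becomes 0.05 × (1 − R²) + 0.19, and power = Φ(0.18/sqrt(2 × variance/50) − 1.96).

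| R² | Variance of OP mean | Reduction | Power | OPs per arm for 80% power |
|---|---|---|---|---|
| 0 | 0.240 | 0% | 45.1% | 117 |
| 0.10 | 0.235 | 2.1% | 45.9% | 114 |
| 0.20 | 0.230 | 4.2% | 46.7% | 112 |
| 0.40 | 0.220 | 8.3% | 48.4% | 107 |
| 1 (ceiling) | 0.190 | 20.8% | 54.2% | 93 |

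**Plausible R².** The number of OPs behind the extract is not given. As an assumption, spread 4443 records evenly over the 350 OPs now at the OHS: 4443/350 = 12.7 records each (the match with the 12.7-day target is coincidence). The reliability of such a history is 12.7 × 0.05/(1 + 11.7 × 0.05) = 0.40. Multiplied by the squared correlation of OP effects over time, R² is 0.40 at correlation 1, 0.20 at 0.7 and 0.10 at 0.5.

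**Sensitivity to records per OP.** With 5 records, reliability is 0.21 and the reduction is 1.1 to 4.3% for time correlations of 0.5 to 1. With 30 records, reliability is 0.61 and the reduction is 3.2 to 12.8%.

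**The case against.** The strongest reply is that nothing here is wrong. Randomising about 100 OPs and analysing with a multilevel model is conventional and valid, and a gain of one to three power points changes no conclusion. This stands, and it limits the point to an improvement.

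Three stronger readings are tempting, and the documents support none of them.

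- **That the allocation is unstratified.** The article is silent. It is a condensed account, and strata may be named in the full protocol.
- **That every participating OP's history is on file.** The extract ends in 2007 and inclusion starts in December 2009. Nothing shows that the consenting OPs appear in it, or with how many records. It also counts days of the first recurrence episode only, whereas the trial outcome is cumulative days, so its predictive value may be lower than the reliability suggests.
- **That chance imbalance between OPs distorts the result.** An SD of 0.045 is a quarter of the planned 0.18, but it is ordinary sampling error, already inside the standard error of 0.098.

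It can also be said that OP diversity is partly handled, because company size and sector are recorded at baseline (Prognostic measures) and may be adjusted for. That is true only if they happen to differ significantly.

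What survives rests on stated text, not on silence: the timing of randomisation, the existence of OP-linked data, and a covariate rule driven by significance tests.

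**Conclusion.** The point holds as a modest, low-priority gain in precision. The article describes no use of OP-level history in the allocation, and its stated covariate rule is inferior to naming predictors in advance. The expected benefit is a variance reduction of 2 to 8%, worth about 2 to 9% more OPs (0.240/0.235 = 1.02; 0.240/0.220 = 1.09), with power moving from about 45% to 46-48%. It would not repair the power: even at the ceiling, power is 54%.

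The range rests on the stated ICC and cluster size, about 12.7 records per OP, a correlation of OP effects over time between 0.5 and 1, a similar ICC for first-episode and cumulative days, and registry coverage of the participating OPs. The last four are not established by the article.

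**What to change.** **Statistical analyses.** For the primary model, replace the significance-driven rule with prespecified OP-level fixed terms: mean recurrent absence days in the registry before the trial where available, a category for OPs without history, region, and company-size mix. Fix these before outcome data are seen. This part remains possible even if the OPs have already been randomised.

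**Randomisation and treatment allocation.** If the full protocol does not already balance the OPs, use stratified or covariate-constrained 1:1 allocation on the same variables. If it does, one sentence in the article should say so. The independent researcher can stay blind to identity by working from coded OP numbers.

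**Cost.** Someone must prepare the coded OP file from the registry, and a rule is needed for OPs without records. The model gains a few OP-level terms against 100 OPs. Recruitment, data collection and treatment do not change.

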### Blinding

Validity can be threatened if employees in the intervention and control group would know about the other group. Because this study is a pre-randomised trial, in which the employees are already randomised before informed consent is given, different information about the study can be provided to the intervention and control group [32]. To ensure that employees are not aware and stay unaware of the two study conditions, the OPs are requested not to talk about this with the employees. Whereas employees are blinded for treatment allocation, blinding of allocation for OPs is not possible because they will know if they are trained in the intervention or not.

### Primary outcome

The primary outcome measure is a relapse of sickness absence, measured as cumulative recurrent sickness absence days. A relapse is defined as a 30% decrease in working days per week or a decrease of at least one day per week because of sickness absence. Recurrent sickness absence days are operationalised as days of sickness absence among employees who have worked a steady amount of days during the first two weeks after they have returned to work. This information will be obtained by record linkages with the sickness absence registry of the OHS and by the employee questionnaires.

### Secondary outcomes

#### Mental health problems

The Four-Dimensional Symptom Questionnaire (4DSQ) is used to measure symptoms of distress, depression, anxiety, and somatisation. The 4DSQ is a self-report questionnaire of 50 items and measures distress, depression, anxiety, and somatisation. The 4DSQ has been validated in a primary care and working population [33,34].

The HADS is a 14-item self-report questionnaire used to measure depression (7 items) and anxiety (7 items) [35]. The questionnaire can be used in somatic, psychiatric, and primary care patients, as well as in the general population [36] and in working populations [37]. The HADS has been validated in different groups of Dutch subjects [38].

#### Work functioning

Work functioning is measured by the Work Role Functioning Questionnaire (WRFQ) [39,40]. The questionnaire has been cross-culturally adapted and translated into Dutch and pre-tested in a working population (Abma et al., submitted for publication). Results of the pre-test showed that the cross-cultural adaptation was successful. The WRFQ measures the perceived difficulties in meeting work demands among employees given their physical health or emotional problems. The WRFQ consists of 27 items divided into five subdomains: 1. work scheduling demands, 2. output demands, 3. physical demands, 4. mental demands, and 5. social demands.

#### Coping behaviour

Coping behaviour is measured by the 19-item version of the Utrecht Coping List (UCL) which assesses coping styles [41]. The questionnaire consists of the following five (coping style) scales: 1. active problem-focussing, 2. seeking social support, 3. palliative reaction pattern, 4. avoidance behaviour, and 5. expression of emotions.

### Economic evaluation measures

Along with the sickness absence data from the OHS's registry system, administrative data of the OHS on consultations of the employee with the OP and company welfare workers is collected. Furthermore, the Trimbos/iMTA questionnaire for Costs associated with Psychiatric Illness (Tic-P), a validated Dutch questionnaire, is used to measure medical consumption and at-work decrements in performance [42]. Finally, an extra item on out-of-pocket costs is added to the Tic-P to calculate medical expenses that are not covered by health insurance.

### Process evaluation measures

A process evaluation is conducted to examine a) the appraisals, attitudes, and activities of OPs, employees, and line managers in the intervention and control group during the treatment period and b) whether OPs adhere to their protocol. OPs who are trained in the intervention, receive a questionnaire before and after the training to examine the quality of the training and the skills and attitudes of the OPs. For the intervention group, a questionnaire is developed for the OP and the employee at baseline. These questionnaires contain items on readiness for change concerning the intervention. At 3-months follow-up, the employees and the OPs in both the intervention and control group receive a questionnaire about the process of treatment during the first three months of return-to-work. The questions elaborate on what was discussed during the consultations, whether assignments were given, which assignments were made, satisfaction with the treatment, and communication between the employee, OP, and line manager. For the intervention group, a questionnaire is also developed for the line manager. The line manager receives a questionnaire on readiness for change before a meeting takes place with the employee as part of the intervention. At 3-months follow-up, the line manager receives a second questionnaire with the same questions as the questionnaires at 3 months for the employee and the OP.

### Prognostic measures

Research on prognostic variables for a relapse of sickness absence has only been conducted in a few studies. For this reason, a range of variables is included in this study to investigate prognostic factors for a relapse of sickness absence. At baseline, the following variables are measured: personal characteristics (e.g. age, gender, marital status, educational level, and physical health), job characteristics (e.g. tenure, size of the company, sector, profession, contract type, number of contract hours before and after sickness absence, and work accommodations after return-to-work), and psychosocial work characteristics (job demands, decision latitude, social support [43,44], job insecurity, conflicts, emotional load [45], work engagement [46], and expectancy to stay-at-work).

### Statistical analyses

Due to the multilevel design of the study (i.e. employees are nested in OPs), multilevel regression analyses will be performed according to the intention-to-treat principle. Per protocol analyses will be conducted to explore if deviations from the protocol have caused bias. Descriptive statistics will be used to measure differences in baseline characteristics between the intervention and control group. In case of significant differences, these will be controlled for in the effect evaluations.

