#### Effect evaluation

The primary outcome variable "cumulative recurrent sickness absence days during follow-up" will be compared between the intervention and control group in the multilevel regression analyses. Time until a relapse of sickness absence will be examined by using Cox proportional hazard analysis to estimate hazard ratio's for a relapse and the 95% confidence interval. In case no software is available to conduct these analyses in a multilevel structure, cluster level survival analyses will be conducted with means for each cluster. In these analyses, cluster size will be introduced as a weighting factor. To investigate differences between the intervention and control group in changes (improvement) on all secondary outcomes, multilevel longitudinal analysis will be used. Pre-planned subgroup analyses on type of CMD, line manager participation in the study, size of the company, perceived decision latitude, type of work, and expectancy to stay-at-work will be conducted.

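### Adjustment covariates are selected by significance of baseline differences, a criterion that ignores prognostic value and guards poorly against recruitment imbalance

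*Protocol article*

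**What the plan says.** Under Statistical analyses, the protocol article describes a two-step procedure. First, "Descriptive statistics will be used to measure differences in baseline characteristics between the intervention and control group". Second, "In case of significant differences, these will be controlled for in the effect evaluations". It names no test and no significance level for this step.

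The rule feeds the effect evaluations. Under Effect evaluation, cumulative recurrent sickness absence days "will be compared between the intervention and control group in the multilevel regression analyses", and no covariate is named there. Randomisation and treatment allocation describes no stratification or matching of OPs whose factors would enter the model by design.

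Under Prognostic measures, "a range of variables is included in this study to investigate prognostic factors for a relapse of sickness absence". That list serves a separate prognostic aim and is not offered as an adjustment set.

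Two design features bear on the point. Under Blinding, "the employees are already randomised before informed consent is given", and OPs cannot be blinded to their own arm. Under Recruitment of participants, those same OPs check eligibility and invite the employees. Methodological considerations concedes that selection by OPs may cause bias.

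**The concern.** A baseline variable distorts the treatment comparison only if it both differs between arms and predicts the outcome. The rule looks at the first condition alone, and through a test whose sensitivity depends on sample size. Three things follow.

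- Variables unrelated to absence days can enter the model by chance.
- Strong predictors with a moderate, non-significant imbalance are left out by this rule. Predictors that happen to be balanced are left out too, and the precision they would have given is lost.
- The content of the primary model is settled only once baseline data have been compared by arm.

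In an individually randomised trial with concealed allocation, baseline differences would be chance alone. Here an OP who knows the arm decides whom to invite, so differences may be systematic. A filter that misses most moderate shifts is then a weak defence.

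**Working it through.** **Inputs from the Sample size section.** "at alpha = 0.05 and ICC = 0.05, 50 OPs, each providing five employees, need to be included in each group", so 250 employees per arm. "For this multilevel power calculation, an effect size of 0.18 was taken into account".

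**Reproducing the plan's figures.** 0.25/1.4 = 0.179, which rounds to the stated 0.18. As a correlation, 0.179/√(0.179² + 4) = 0.0896, in line with "which resulted in a correlation of 0.09". The design effect is 1 + (5 − 1) × 0.05 = 1.20. The article states no figure for the covariate rule and no power.

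**Assumptions (the article gives none of these).** A 5% two-sided level for the baseline tests; independence of those tests; a covariate ICC of 0 or 0.05; the covariate–outcome correlation; the size of any recruitment shift.

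**1. Chance entries.** Prognostic measures names 20 or 21 variables: 5 personal, 7 or 8 job (contract hours before and after absence counted once or twice) and 8 psychosocial. The secondary outcomes add 16 scales: 4DSQ 4, HADS 2, WRFQ 5, UCL 5.
- 20 tests: 20 × 0.05 = 1.0 expected; P(at least one) = 1 − 0.95²⁰ = 64%.
- 37 tests: 37 × 0.05 = 1.85 expected; P(at least one) = 1 − 0.95³⁷ = 85%.

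**2. What the filter can see.** The SE of a standardised baseline difference is √(2 × 1.20/250) = 0.098 with covariate ICC 0.05, or √(2/250) = 0.089 with ICC 0. The flagging threshold is 1.96 × SE = 0.192 or 0.175 SD. An observed 0.15 SD imbalance has z = 0.15/0.098 = 1.53, p = 0.13 (or p = 0.09 with ICC 0), and is ignored either way.

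**3. Expected bias left by a true shift.** Let the observed difference be D ~ N(μ, SE²) and let c be the threshold. When D is flagged, adjustment removes the bias; when it is not, ρ × D remains. So expected bias = ρ × {μ[Φ(b) − Φ(a)] + SE[φ(a) − φ(b)]}, with a = (−c − μ)/SE and b = (c − μ)/SE.

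Take μ = 0.15, ρ = 0.4 and SE = 0.098. Then b = 0.43, a = −3.49, and P(not flagged) = 0.666, so the shift is flagged 33% of the time. The bracket is 0.15 × 0.666 + 0.098 × (0.001 − 0.364) = 0.064. The bias is 0.4 × 0.064 = **0.026 SD**, and 0.026/0.18 = 14%. With SE = 0.089 the shift is flagged 39% of the time and the bias is 0.023 SD. With no adjustment the bias would be 0.4 × 0.15 = 0.06 SD; with pre-specified adjustment it is about 0.

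**4. Simulation.** 4,000 runs per scenario, 100 OPs with 5 employees each, ICC 0.05, one covariate.

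| Scenario | Unadjusted | Protocol rule | Always adjusted |
|---|---|---|---|
| Power, effect 0.18, correlation 0.3 | 45% | 45% | 48% |
| Power, effect 0.18, correlation 0.5 | 46% | 46% | 56% |
| Power, effect 0.18, correlation 0.7 | 49% | 51% | 73% |
| Type I error, no shift, correlations 0.3 to 0.7 | 4.4–5.1% | 3.8–4.6% | 4.5–5.0% |
| Bias, shift 0.1 SD, correlation 0.5 | 0.051 | 0.029 | 0.001 |
| Bias, shift 0.2 SD, correlation 0.5 | 0.099 | 0.020 | −0.001 |

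In the last two rows, where the true effect is zero, the rejection rates under the rule were 5.6% and 6.0%, against 5.2% and 5.3% with constant adjustment.

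**The case against.** The strongest defence is that the rule does limited harm, and much of that stands.

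- **Invalid inference.** A reader might infer that model selection makes the confidence interval or p-value anti-conservative. The calculations do not support this. The rule looks at baseline data, not outcomes, and under pure randomisation the simulated type I error is slightly below nominal.
- **A large bias.** A reader might take 0.4 × 0.15 = 0.06 SD, a third of the target effect, as the bias. That is the error given one particular unflagged imbalance. If the imbalance arose by chance, it is sampling variation that the unadjusted standard error already covers. If it is systematic, the rule sometimes catches it, and the expected residual is about 0.026 SD.
- **Chance entries.** One or two non-prognostic covariates among 500 employees cost almost nothing. The article does not say that every listed variable and scale will be tested, so the count is an upper guide.
- **Sample-size equivalent.** If covariates explain 10–20% of the variance, 500/(1 − R²) − 500 gives 56 to 125 employees. That compares full adjustment with none, not with the rule, and the R² is unsupported by the article.
- **Missing detail.** An article need not list covariates, and it does not say that adjustment is confined to flagged variables. But the objection here is to a rule that is stated, not to an omitted list, and nothing elsewhere in the article withdraws it.
- **Systematic imbalance is not demonstrated.** Methodological considerations describes selection as possible in both groups; that it differs between arms is an inference from unblinded recruitment after allocation. It makes a shift plausible, not established.

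**Conclusion.** The point holds. Significance of a baseline difference is a poor criterion for choosing covariates, and it leaves the primary model open until the arms have been compared at baseline. The harm is moderate: lost precision and incomplete protection against recruitment imbalance, not inflated type I error under randomisation.

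The size depends on assumed correlations and shifts. The power forgone relative to pre-specified adjustment is about 3 percentage points at correlation 0.3 and 10 at 0.5. The expected residual bias is about 0.02 to 0.03 SD for shifts of 0.10 to 0.20 SD at correlations of 0.4 to 0.5. If the available covariates predict absence days only weakly, both figures shrink towards nothing. The change should be made because it is nearly free and because OPs recruit knowing their arm.

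**What to change.** Delete the significance rule. Before any comparison of data by arm, fix a short covariate set on prognostic grounds from variables already collected, and include it in the primary model whatever the observed imbalance. Age, gender, type of CMD, company size and baseline 4DSQ distress are examples. The article gives no evidence that these are the strongest predictors, so the choice belongs to the investigators. Report baseline balance descriptively, without tests; looking at balance remains useful here because of how employees are recruited. Keep adjustment for other observed imbalances as a sensitivity analysis.

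The cost is a change of wording and a few degrees of freedom among 500 employees. No new data are needed for the examples named. The gain is small if the chosen covariates turn out to be weakly prognostic, and adjustment cannot remove selection on characteristics that were not measured.
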